### Secondary outcomes

The secondary outcomes of this study will include the following:The number of participants who survive thrombocytopenia at the seventh day after randomization.The total amount of platelets transfused into participants during the observational period.The time to recovery to a normal platelet level.The occurrence of bleeding events.

In this study, the normal platelet level is defined as PCs not less than 100 × 10^9^/L. Time to recovery to a normal platelet level is calculated from the date of randomization to the date when PCs >>100 × 10^9^/L.

### Data management

A case report form (CRF) is used for each patient to collect the data. Assessments are made at the screening period, inclusion (D0) and on days 1 to 7. Assessments include sepsis-related organ failure assessment, monitoring (catheter, tubes and drains, mechanical ventilation procedures), laboratory tests (hematology, biochemistry, urinalysis, pregnancy test at inclusion only), and microbiology (blood cultures, mycology). Data on adverse events, compliance and concomitant treatments are collected at each visit. We will determine vital status among survivors at 28 days following randomization through chart review and direct contact with patients if necessary. Participants will be evaluated every day till the seventh day after randomization. Physicians and research nurses who are not involved in the patients’ care will assess the outcome.

All documents collected in this study will be stored safely in confidential conditions. On all study-specific documents, other than the signed consent, the participant will be referred to by the study participant number/code, not by name. Study documentation will be archived for a period of 5 years after the study.

### Adverse events

All adverse events will be recorded and closely monitored until resolution or stabilization or until it has been shown that the study treatment is not the cause of the event. The chief investigator will be informed immediately of any serious adverse events and will determine (in cooperation with the treating medical practitioners) the seriousness and causality of these events.

All treatment-related serious adverse events will be recorded and reported to the research Ethics Committee as part of the report. Unexpected serious adverse events will be reported to the research Ethics Committee within the relevant time frames. The chief investigator will be responsible for all adverse event reporting. All site staff will be appropriately trained in the procedures to follow and the forms to use during the study protocol prior to study initiation. Regular central monitoring for all studies and site monitoring, as determined by the trial-specific risk assessment, will be used to ensure that all adverse events are identified and acted on appropriately.

## Statistical analysis

### Sample size and statistical analysis

The all-cause mortality of sepsis varies in different patient populations. The mortality of 28-day ranges from 20.8% to 61% but no reliable 7-day mortality has been reported to our knowledge [12, 13]. Using the 28-day mortality in our center, we assumed that the 7-day mortality is 40%. Our sample size was calculated to detect a 10% difference in mortality at day 7 between the two groups with a two-tailed test, a significance level (alpha) of 5% and a power of 80%. We plan to include a total of 708 subjects.

### Type of analysis

We will utilize an intention-to-treat approach to examine differences in the mortality in the two groups in the primary analysis by the Pearson χ2 test. Safety parameters and secondary efficacy parameters will be analyzed using the Pearson χ2 test and logistic regression (if necessary). Cox proportional hazards models and the Kaplan-Meier method will also be applied. Adverse events will be tabulated according to randomized group assignment and the proportions will be compared using Fisher’s exact test.

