### Study design

The study is designed as a randomized, open-label, placebo-controlled, multi-center study in 17 tertiary academic medical centers. The sites that are participating in this study are medical, surgical or emergency ICUs. Patient enrollment is expected to last up to 18 months. The end of the study is defined by the last follow-up of the last enrolled patient. The trial is registered at clinicaltrials.gov (NCT02094248).

Qualified patients will be randomized into either of the two groups: the intervention group and the control group. Both groups receive standard care and will receive appropriate medical support based on guidelines issued by the surviving sepsis campaign [1].

The intervention group will receive administration of rhTPO (TPIAO™, Shenyang Sunshine Pharmaceutical Company Limited (SUNSHINE), Shenyang, China). The rhTPO will be subcutaneously injected in the intervention group after randomization. The dose is 15,000 U per day. The subcutaneous injection will be terminated when PCs are increased by 50 × 10^9^/L for 2 consecutive days compared with PCs at baseline. The duration of rhTPO will be 7 days. Time from randomization to administration of rhTPO will be within 24 hours.

Patients in the control group will receive the equal amount of normal saline, which will be subcutaneously injected as a placebo. The normal amount of saline is 1 ml per day for the initial stage and the maintenance stage. The subcutaneous injection will be terminated after 7 days. Time from randomization to administration of placebo will also be within 24 h.

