### Randomization

Patients will be randomized after informed consent is obtained and it is confirmed that all inclusion and no exclusion criteria are met, prior to the patient-clinician discussion of treatment options and patient risk. Allocation will be based on a 1:1 ratio between the intervention and control groups. The allocation sequence will be generated by utilizing the ResMan Research Manager central randomization clinical trial management public platform (http://www.medresman.org/). The randomization will be stratified by study site. On the day of inclusion, investigators will log information into the web database using user identifications and passwords to obtain the randomization numbers and allocated groups for the eligible patients. Both investigators and participants will be aware of the allocations.

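### The primary mortality test ignores the site stratification and the baseline organ failure score, which gives up efficiency but not validity

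*Protocol article*

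**What the plan says.** - **Allocation** (protocol article, Randomization): "Allocation will be based on a 1:1 ratio between the intervention and control groups", and "The randomization will be stratified by study site". Site is the only stratification factor named.
- **Sites** (Study design): a "multi-center study in 17 tertiary academic medical centers". On their type: "The sites that are participating in this study are medical, surgical or emergency ICUs".
- **Primary test** (Type of analysis): the plan is to "examine differences in the mortality in the two groups in the primary analysis by the Pearson χ2 test", by intention to treat. No strata or covariates are named.
- **Models** (Type of analysis): "Safety parameters and secondary efficacy parameters will be analyzed using the Pearson χ2 test and logistic regression (if necessary"). Cox and Kaplan-Meier methods are also mentioned, again without strata or covariates.
- **Baseline severity** (Data management): inclusion (D0) is one of the assessment times, and "Assessments include sepsis-related organ failure assessment".
- **Sample size** (Sample size and statistical analysis): 708 patients, to detect a 10-point difference in day-7 mortality from an assumed 40%, with two-sided alpha 5% and power 80%.

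**The concern.** When allocation is balanced within site, differences in mortality between sites no longer contribute to the sampling error of the treatment comparison. The variance in the unstratified Pearson test still contains them. The standard error is then larger than the design warrants, p-values run slightly large, and an interval built the same way runs slightly wide.

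Baseline severity is a separate matter. It is not a stratification factor, so omitting it leaves alpha where it should be, but a covariate that predicts death could sharpen the comparison.

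Power is at stake. The trial is sized with no margin, and the article says that no reliable 7-day mortality figure was available to plan from.

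**Working it through.** **1. Reproduce the plan's figure.** Inputs from the article: 40% against 30% (the 10-point difference taken as a reduction), two-sided 5%, power 80%, 1:1.

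n per arm = [p1(1−p1) + p2(1−p2)] × (1.960 + 0.842)² / d² = (0.24 + 0.21) × 7.849 / 0.01 = 353.2, rounded up to 354, so 708 in total. This matches. With 354 per arm, the power of the plain comparison (pooled-variance formula) is 79.8%. That corresponds to a standardized effect of 1.960 + 0.834 = 2.794.

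**2. Effect of ignoring site.** The documents give no between-site variance, so it is an assumption, shown as a range. Let R² be the share of outcome variance due to site, computed for normal site effects on the logit scale around a mean rate of 35%. With balance within site:

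- true alpha of Pearson = 2 × [1 − Φ(1.960/√(1−R²))]
- power of Pearson = Φ((2.794 − 1.960)/√(1−R²))
- power of a site-stratified test = Φ(2.794/√(1−R²) − 1.960)

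| Site SD (logit) | R² | SD in points, √(R² × 0.35 × 0.65) | True alpha, Pearson | Power, Pearson | Power, stratified | Gain (points) |
|---|---|---|---|---|---|---|
| 0.2 | 0.009 | 4.5 | 4.9% | 79.9% | 80.1% | 0.3 |
| 0.3 | 0.020 | 6.7 | 4.8% | 80.0% | 80.6% | 0.5 |
| 0.5 | 0.052 | 10.8 | 4.4% | 80.4% | 81.8% | 1.4 |
| 0.8 | 0.117 | 16.3 | 3.7% | 81.3% | 84.4% | 3.2 |

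Gains are taken before rounding. Worked row for SD 0.5: √(1 − 0.0517) = 0.974; 1.960/0.974 = 2.013, alpha 4.4%; 2.794/0.974 − 1.960 = 0.909, power 81.8%.

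**3. Check by simulation.** In 40,000 simulated trials per setting, site rates were drawn around 40% with an SD in percentage points.

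| Site SD (points) | Alpha, Pearson / Mantel-Haenszel | Power, Pearson / Mantel-Haenszel |
|---|---|---|
| 0 | 4.9% / 4.9% | 80.3% / 80.3% |
| 8 | 4.8% / 5.0% | 79.9% / 80.6% |
| 12 | 4.4% / 5.0% | 80.5% / 82.0% |
| 15 | 4.0% / 5.0% | 81.4% / 83.7% |

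The pattern is the same: no gain when sites are alike, and 2.3 points (83.7 − 81.4) at the largest spread.

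**4. Adding baseline severity.** The prognostic strength of the score is also an assumption. Simulation used 17 near-equal sites, blocks of 4 within site (assumed) and 6,000 trials per setting. The adjusted test was a least-squares regression of death on treatment and severity within site.

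| Site SD, severity SD (logit) | Pearson | Site only | Site and severity |
|---|---|---|---|
| 0.3, 0.5 | 80.7% | 81.2% | 83.0% |
| 0.5, 0.8 | 80.0% | 81.1% | 85.1% |
| 0.5, 1.0 | 80.4% | 81.4% | 87.1% |

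The simulation error of each power figure is about √(0.8 × 0.2/6000) = 0.5 points. Under no effect, the fully adjusted test rejected in 4.9% to 5.4% of trials. A separate run of 4,000 trials per setting, using logistic regression on treatment and severity without site, gave 81.1%, 84.8% and 86.0% in the same three settings. Most of the gain therefore comes from severity.

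**The case against.** The strongest reply is that nothing here is wrong. The sample size was computed for an unadjusted comparison, the planned test is that comparison, and it delivers about the planned 80% in every setting above. A prespecified unadjusted test of mortality is legitimate and easy to explain. This stands, and it limits the point to efficiency and agreement between design and analysis.

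Four further limits also stand:

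- **Size of the site effect.** The article's statement that "The mortality of 28-day ranges from 20.8% to 61" per cent might be read as evidence of that spread among these sites. It is not: the range concerns 28-day mortality across published populations, whereas the trial is sized on day 7. With 17 sites, an SD of 12 points already implies lowest and highest sites near 20% and 62%, so the larger settings are upper-end. Mixed ICU types make some variation likely but do not give its size.
- **Balance within site.** The conservatism requires it, for instance through blocks. The article states stratification without giving the scheme. With no such balance, Pearson would hold its nominal alpha, and adjustment would still gain power.
- **Severity and alpha.** A reader might infer that ignoring severity also makes the test conservative. It does not, because severity is not a stratifier.
- **Severity gain.** No document gives the prognostic strength of the score, so 83% to 87% is illustrative.

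A final reply is that an unseen analysis plan may add adjusted analyses. It may, but this article names the primary test, so a different primary test elsewhere would contradict it.

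**Conclusion.** The point holds as a free improvement. The primary test does not reflect the stratified allocation and leaves a collected baseline score unused. Ignoring site costs about 0 to 3 points of power and lowers true alpha to somewhere between 4.9% and 3.7%, for an assumed between-site logit SD of 0.2 to 0.8 and balance within site. Adjusting for severity as well brings the total gain to about 2 to 7 points under the assumed effects.

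A reader might go further and conclude that the trial is underpowered or its result unreliable. The documents do not support that: 708 is reproduced exactly, power stays at about 80%, and the error is only towards caution.

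**What to change.** By formal amendment, make the primary mortality analysis a logistic regression with treatment, site and the D0 organ failure score, for both primary time points. Report the marginal (standardized) risk difference with its 95% confidence interval. State in advance the rule for pooling small sites, and that the score used is the one recorded before the first study injection. If a model is not wanted, the minimum alternative is a Cochran-Mantel-Haenszel test stratified by site. Keep the unadjusted Pearson test as a sensitivity analysis.

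The amendment should be settled before outcomes by arm are examined. The trial is unblinded and recruiting, and an adjusted model chosen later would be open to challenge.

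The cost is a short change to the Type of analysis section and the amendment procedure, with no new data. The downside is that sites average only 708/17 ≈ 42 patients, so some may need pooling.

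### Time to platelet recovery: a Kaplan-Meier curve that censors deaths would overstate the proportion recovered, and the protocol does not say how deaths before recovery are handled

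*Protocol article*

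**What the plan says.** Under Type of analysis, the protocol article gives the primary mortality comparison to the Pearson chi-square test, and safety and secondary efficacy parameters to the chi-square test with logistic regression if needed. The next sentence is: "Cox proportional hazards models and the Kaplan-Meier method will also be applied". It names no outcome and no censoring rule.

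Under Secondary outcomes, one outcome is a duration: "Time to recovery to a normal platelet level is calculated from the date of randomization to the date when PCs" pass 100 × 10^9/L. Nothing is said about patients who die before that date.

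Under Data management: "Participants will be evaluated every day till the seventh day after randomization". Vital status is also determined at day 28.

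Under Sample size and statistical analysis: "Using the 28-day mortality in our center, we assumed that the 7-day mortality is 40" per cent, and "Our sample size was calculated to detect a 10% difference in mortality at day 7 between the two groups".

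**The concern.** Kaplan-Meier and Cox are the only time-to-event methods named. They follow directly on the sentence about secondary efficacy parameters, and only one outcome is defined as a time. The natural reading is that they serve time to platelet recovery.

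For that outcome, death is a competing event and not ordinary loss to follow-up. If deaths are censored, which is the usual default, the curve assigns to each patient who died the later recovery experience of those still under observation. One minus the Kaplan-Meier estimate (1-KM) then exceeds the proportion who actually recover. This happens whether or not poor recoverers are the ones who die. The Background section links falling platelet counts to mortality, which makes it harder still to treat the censoring as harmless.

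What is at stake is the reported proportion recovered by day 7 and the visual comparison of the arms. The size of the error depends on mortality, which the drug is hoped to reduce, and on recovery, which it is hoped to raise. The arms need not be distorted equally.

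**Working it through.** **Inputs from the protocol article**
- 7-day mortality 40%, difference 10 points, "with a two-tailed test, a significance level (alpha) of 5% and a power of 80" per cent (Sample size and statistical analysis).
- "We plan to include a total of 708 subjects" (same section) and "Allocation will be based on a 1:1 ratio between the intervention and control groups" (Randomization), hence 354 per arm.
- Daily evaluation to day 7 (Data management).

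**Assumptions, because the documents give no figure**
- True recovery by day 7 between 20% and 50%.
- Constant hazards of recovery and of death over the 7 days.

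**Step 1: reproduce the plan's own figure.** For 40% against 30%, unpooled variance:

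n per arm = (1.960 + 0.842)² × (0.40×0.60 + 0.30×0.70) / 0.10² = 7.849 × 0.45 / 0.01 = 353.2, rounded up to 354, total 708.

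This matches. With 40% against 50% the total would be 770 (unpooled) or 776 (pooled), so the difference is read as a reduction to 30%.

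**Step 2: 1-KM against true recovery.** Let R be the true proportion recovered by day 7 and D the proportion who die before recovery.
- Cumulative total hazard: H = -ln(1 - R - D)
- Recovery part: H × R / (R + D)
- 1-KM with deaths censored = 1 - exp(-H × R / (R + D))

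Example, R = 40% and D = 40%: H = -ln(0.20) = 1.609; recovery part 0.805; 1-KM = 1 - exp(-0.805) = 55.3%, an excess of 15.3 points.

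Excess of 1-KM over true recovery, in percentage points:

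| Die before recovery | R = 20% | R = 30% | R = 40% | R = 50% |
|---|---|---|---|---|
| 10% | 1.2 | 1.8 | 2.6 | 3.4 |
| 20% | 2.5 | 4.0 | 5.7 | 7.7 |
| 30% | 4.2 | 6.8 | 9.7 | 13.4 |
| 40% | 6.3 | 10.3 | 15.3 | 22.2 |

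The 40% row is an upper bound at the plan's mortality. Deaths after recovery do not compete, and the 40% is itself taken from 28-day mortality, which 7-day mortality in the same patients cannot exceed.

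**Step 3: between arms, equal recovery hazards.** Take a recovery hazard of 0.10 per day in both arms, and death hazards that are the same before and after recovery and match 7-day mortality:
- Control: -ln(0.60)/7 = 0.0730 per day
- Intervention: -ln(0.70)/7 = 0.0510 per day

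True recovery = r/(r + d) × (1 - exp(-7(r + d))), where r and d are the recovery and death hazards.

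| | True recovery | 1-KM | Excess |
|---|---|---|---|
| Control | 40.6% | 50.3% | 9.8 |
| Intervention | 43.2% | 50.3% | 7.1 |

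The curves coincide although the true proportions differ by 2.6 points. Over recovery hazards of 0.05 to 0.20 per day, the excess is 6.1 to 12.9 points in control and 4.4 to 9.4 in the intervention arm.

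**Step 4: between arms, unequal recovery.** From the table in step 2, a control arm with R = 20% and D = 40% has an excess of 6.3 points, and an intervention arm with R = 50% and D = 30% has 13.4. Here the arm with fewer deaths is overstated more.

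**The case against.** The strongest objection is that the faulty analysis is inferred. The sentence names no outcome. Kaplan-Meier and Cox are ordinary supporting analyses for mortality to day 28, where no competing event arises. Nor does the text say that deaths would be censored: if patients who die are kept at risk as not recovered to day 7 and follow-up is otherwise complete, 1-KM equals the cumulative incidence. Such detail may sit in an analysis plan that is not shown. There is also a separate day-7 outcome that counts patients free of thrombocytopenia, so the proportion recovered need not be read from a curve.

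These points stand as limits. A reader might infer that the protocol commits to censoring deaths; it does not. Even so, the article names methods, and no other named method can analyse its one duration outcome. Chi-square, logistic regression and Fisher's test compare proportions. A count of status at day 7 does not replace an analysis of time to recovery.

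Two stronger readings also fail. One is that the Cox result is biased as well. A Cox model that censors deaths estimates the cause-specific hazard ratio, which is valid as such; it simply does not translate directly into a proportion recovered. The other is that the arm with more deaths is always flattered more. That holds with equal recovery hazards, but step 4 shows the reverse when recovery differs enough.

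**Conclusion.** The point holds for one secondary outcome. Kaplan-Meier appears intended for time to recovery, and if deaths are censored the curve overstates recovery: by about 6 to 22 points if 40% die before recovery, and by about 2.5 to 8 points if 20% do, for true recovery of 20 to 50%. The direction of the overstatement is certain. Its size rests on assumed recovery rates and constant hazards, and 40% is a ceiling. The arms are affected unequally when mortality or recovery differs, and which arm gains more depends on both.

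The defect is the unstated target and handling of death, together with a named method that fits this outcome poorly under its usual default. The chi-square analysis of mortality and the total of 708 are untouched. This is a worthwhile, inexpensive improvement and not a threat to the trial's main conclusion.

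**What to change.** State which outcome each time-to-event method serves:
- Analyse time to platelet recovery by cumulative incidence (Aalen-Johansen), with death before recovery as a competing event and administrative censoring at day 7.
- Compare the arms with Gray's test or a Fine-Gray model.
- Report the cause-specific Cox hazard ratio for recovery alongside.
- Keep Kaplan-Meier for survival to day 28.

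The cost is a few sentences and standard software. No new data are needed: platelet counts are followed daily to day 7, and deaths must be dated for the primary outcome in any case. There is one small downside. The subdistribution hazard ratio from Fine-Gray partly reflects mortality, so it must be read beside the cause-specific ratio.

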## Ethics

### Declaration of Helsinki

The research team will ensure that this study is conducted in accordance with the principles of the Declaration of Helsinki [14].

### Ethics committee and regulatory approval

The trial will also be conducted in accordance with the national ethics review for biomedical research involving humans (Trial) [15]; and international ethical guidelines for biomedical research involving human subjects [16].

The protocol, informed consent form, participant information sheet, any further patient documents and any proposed advertising material were submitted to the Institutional Review Board (IRB) of the Ethics Committee of Jinling Hospital for written approval. The research team has obtained approval from the Ethics Committee of Jinling Hospital for all substantial amendments to the original approved documents (approval number 2014SY-079).

### Protocol amendments

Any modifications to the protocol that may impact on the conduct of the study, the potential benefit of the patient or may affect patient safety, including changes of study objectives, study design, patient population, sample sizes, study procedures, or significant administrative aspects will require a formal amendment to the protocol. Such amendments will be agreed upon by the sponsor, and approved by the Ethics Committee prior to implementation and notified to the health authorities in accordance with local regulations.

Administrative changes of the protocol are minor corrections and/or clarifications that have no effect on the way the study is to be conducted. These administrative changes will be agreed upon by the sponsor, and will be documented in a memorandum. The Ethics Committee may be notified of administrative changes.

